### Measures

#### Baseline

The primary outcomes for this feasibility study are rates of eligibility, recruitment, intervention delivery, and participant retention at follow-up. Eligibility will be established by midwives using a checklist of inclusion and exclusion criteria and the AUDIT-C. Rates of recruitment, intervention delivery, and retention will be determined from case report forms. The alcohol counselor will record whether the alcohol intervention was delivered with the participant.

The trial will also measure the proposed outcomes for a future main trial, allowing us to test the usefulness of measures, obtain an estimate of variability to inform power calculations, and assess the acceptability of trial documents. The primary outcome in a full trial will be the maximum number of standard drinks (units) per drinking occasion during the pregnancy, a continuous measure), with secondary outcomes including alcohol abstinence (binary) in the third trimester and 6 months post-partum. Participants will be asked to complete a questionnaire containing three baseline measures, with their midwife’s assistance if requested.

1 The Timeline Follow-Back (TLFB) questionnaire [39] measures alcohol consumption during pregnancy for two weekly periods. The respondent is asked to complete a simple diary (with visual cues) detailing alcohol use in the preceding week. The preceding week might not be typical (for example, a patient might have reduced their drinking as the booking appointment approached), and there may be a tendency to enhance social desirability in responses. Thus, a second diary is requested covering the heaviest drinking week since becoming pregnant. The TLFB has been used as an outcome measure with pregnant women [23,24,40] previously. Scores from the 7-day version, which we will use to minimize the burden on patients, have been found to be strongly correlated with those gathered within longer timeframes [41-43].

2 The AUDIT-C is completed in respect of the participant’s drinking in the 6 months before pregnancy, because the quantity and pattern of previous drinking is predictive of whether or not pregnant women drink during pregnancy [44]. In a full trial, this information will establish whether effects of the intervention differed according to the level of pre-pregnancy drinking.

3 The EuroQoL EQ-5D-3 L instrument measuring quality of life will be completed as part of the health-economics analysis (see below).

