#### Follow-up

Six months after a baseline interview (during the third trimester), the project manager ascertains whether the participant has experienced a fetal loss or had pregnancy complications diagnosed since her first trimester. In either case, the participant will be excluded from follow-up data collection and will not be contacted. This information will be sought from the Regional Maternity Survey Office (RMSO; http://www.nepho.org.uk/rmso/) and the community midwife in order to minimize the risk of causing distress to the participant by inappropriate telephone contact. The RMSO is a publicly funded organization supported by clinical staff, which collects information from hospitals across the north of England to monitor health outcomes for mothers and babies. The project administrator contacts participants who still meet the criteria for inclusion in their third trimester to arrange a telephone interview with the project manager (GW). In the interview, the project manager will administer the 7-day TLFB questionnaire, the EQ-5D-3 L, and a NHS service use questionnaire. We will also check whether participant follow-up rates vary based on socio-economic profile and drinking status.

At 6 months after the due birth date of the participant, the project manager will again contact the RMSO to check whether the participant has experienced a stillbirth or loss after birth, and any such cases will be excluded from follow-up data collection without further contact. Birth outcome data (covering birth weight, gestational age at delivery, presence of congenital anomaly and fetal loss, or loss after birth if appropriate) will also be abstracted and recorded on a case report form. The project manager will then follow up eligible participants by telephone to ascertain longer-term follow-up rates. The screening and outcome measurement tools (the TLFB, EQ-5D-3 L & NHS service use questionnaires) will be re-administered, and open response questions will be asked about the acceptability of the instruments.

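### The definitive trial's primary outcome is the largest single drinking occasion in pregnancy, but the diaries are chosen by week and may not contain that occasion

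*Protocol article*

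**What the plan says.** Under Measures, the Baseline section states: "The primary outcome in a full trial will be the maximum number of standard drinks (units) per drinking occasion during the pregnancy". The pilot records the definitive trial's proposed outcomes in order to try out the measures and to "obtain an estimate of variability to inform power calculations". Planned analysis says that the pilot's outcome estimates will feed the full trial's sample size.

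The instrument is the Timeline Follow-Back (TLFB), which "measures alcohol consumption during pregnancy for two weekly periods". The first diary is one "detailing alcohol use in the preceding week". The article warns that "The preceding week might not be typical" and that answers may be shaded towards what is socially acceptable, so "a second diary is requested covering the heaviest drinking week since becoming pregnant". It supports the 7-day form by its correlation with longer recall periods. The other drinking measure at baseline, AUDIT-C, is completed for the six months before pregnancy. No described item asks for the largest single occasion.

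For the third trimester, the Follow-up section says only that "the project manager will administer the 7-day TLFB questionnaire". The Abstract says that the baseline measures, which include both diaries, are taken again at each telephone follow-up.

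**The concern.** The outcome and the second diary are selected by different rules. The outcome is the largest amount on one occasion; the diary is the heaviest week. A week can be heaviest because a woman drank a little on many days, while her largest occasion fell in a lighter week. That occasion is then on no form, and no later analysis can recover it.

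The stated reasons for the diaries do not cover this. An untypical last week and social desirability justify looking beyond the last week. Correlation of 7-day scores with longer periods says nothing about whether a chosen week contains the maximum.

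The pilot is meant to show whether this measure works and to supply its variability. If the diaries record something other than the defined outcome, the mean and SD carried forward describe a different variable, and the mismatch passes into the definitive trial's primary endpoint. The Background section contrasts frequent drinking with binge drinking, and the gap between recorded and true maximum depends on that pattern.

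**Working it through.** **The plan's own figures.** The article gives no mean, SD, effect size or power for this outcome, so there is nothing to reproduce for it. The recruitment figures reproduce and are unaffected: 2,742 × 0.08 = 219.4; × 0.70 = 153.6; × 0.78 = 119.8; × 0.67 = 80.2; × 0.75 = 60.2. The article states 220, 154, 120 and 60.

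**Direction.** Let T be the largest occasion over all weeks in the window, and R the largest occasion within the two diary weeks. R is a maximum over a subset of the same occasions, so R ≤ T when recall is accurate.

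**Example.** A woman drinks 2 units on each of six days in one week (6 × 2 = 12), 9 units on a single day in another week, and nothing last week. Since 12 > 9, the first week is heaviest by total. R = max(2, 0) = 2, while T = 9.

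**Size, by simulation.** Every input is an assumption:
- windows of 10 weeks (booking is before 16 weeks' gestation) and 26 weeks (the third-trimester interview is six months after baseline);
- an average of one drinking day a week, either the same for all women or varying between them (gamma, shape 1.5);
- log-normal units per drinking day, median 2, log-SD 0.5 or 0.8, with none or 30% of the log variance between women;
- perfect recall, and the heaviest week chosen by total.

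| Window | Drinkers whose largest occasion is in neither diary |
|---|---|
| 10 weeks | 18–41% |
| 26 weeks | 26–60% |

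Across both windows the recorded mean is about 4–14% too low. The low ends come from varying rates with log-SD 0.8 and no between-woman variation in units. The high ends come from equal rates with log-SD 0.5 and 30% between-woman variance.

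A second set of assumptions (0.5 to 3 drinking days a week; units per occasion with mean 3 and SD 2, or mean 4 and SD 4) gives 10–40% missed at 8–12 weeks and 18–53% at 28 weeks, with the mean 3–16% low.

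**SD.** At 26 weeks, if every woman has the same rate and the same unit distribution, the recorded SD is higher than the true SD: 1.80/1.58 = 1.14 (log-SD 0.5) and 5.47/5.18 = 1.06 (log-SD 0.8). Once rates vary between women, the change is about −7% to +1%. With 60% of the log variance in units between women, it is −10% and −8%. The second set of assumptions gives an SD 2–7% too low.

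**Preceding-week diary alone.** If all weeks are alike, the largest occasion falls in the last of 26 weeks with probability 1/26 = 3.8%. A last-week diary therefore misses it in 1 − 0.038 = 96% of drinkers. The simulation agrees.

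**The case against.** The strongest reply is that weekly total is a reader's assumption. The article does not say how heaviest is judged. A woman may name the week of her biggest session, and then nothing is lost. The midwife can help with the form, and a journal article may leave its exact wording to the questionnaire. This stands, and it is why the point is that capture is not guaranteed, rather than that it fails. It does not remove the point: with the term undefined, women may apply different rules, and nothing described ties the chosen week to the largest occasion.

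The loss also shrinks when drinking is infrequent or the window is short. At one drinking day a month over 26 weeks, only 7–13% are missed. At 10 weeks with varying rates and no between-woman variation in units, 18–29% are missed and the mean is 4–7% low. The pilot's own primary outcomes (eligibility, recruitment, delivery and retention) are untouched, and trying out the measures is one of its aims.

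A reader might go further and infer that the recorded SD is too high and that a sample size based on it would be 12–30% too large. Those figures are the squares of the two ratios above (1.06² = 1.12; 1.14² = 1.30), so they need every woman to drink at the same rate with the same unit distribution. With variation between women, the excess disappears or reverses. A reader might also infer that an intervention removing isolated binges would show no effect. That is possible in principle, but it was not calculated.

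**Conclusion.** The point holds as a mismatch between a defined outcome and its only described source. If heaviest is read as weekly total and recall is accurate, the error runs one way: the recorded maximum, and so its mean, is too low. Under the assumed patterns, the missed fraction is sizeable (18–41% over 10 weeks, 26–60% over 26 weeks) and the shortfall in the mean moderate (about 4–14%).

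The documents do not support saying that the largest occasion is in fact often lost or that the mean and SD are wrong, because they give no drinking distribution and do not define heaviest. No sample-size error is claimed in either direction.

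The third-trimester wording matters more. If it means the preceding week alone, the pregnancy maximum would be missed in nearly all drinkers. The Abstract suggests that both diaries are repeated, so this needs clarifying; it is not an established omission. The change is worth making now because it is cheap and an unrecorded occasion cannot be recovered.

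**What to change.** At baseline and at the third-trimester interview, add one question asking for the most units drunk on any single occasion in the outcome window: since becoming pregnant at baseline, and since baseline at follow-up. Derive the proposed primary outcome from it, and report its SD as the input to the definitive power calculation. Keep the preceding-week diary as it is.

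Alternatively, define the second diary as the week containing the heaviest single occasion. State in the Follow-up section that it is repeated in the third trimester, and over what period.

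The cost is one more recall question on the form and in the telephone call, and a minor amendment. The new item is open to the same recall error as a diary over the same window. Women already recruited would lack the baseline answer but could still answer at follow-up.

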#### Follow-up

Six months after a baseline interview (during the third trimester), the project manager ascertains whether the participant has experienced a fetal loss or had pregnancy complications diagnosed since her first trimester. In either case, the participant will be excluded from follow-up data collection and will not be contacted. This information will be sought from the Regional Maternity Survey Office (RMSO; http://www.nepho.org.uk/rmso/) and the community midwife in order to minimize the risk of causing distress to the participant by inappropriate telephone contact. The RMSO is a publicly funded organization supported by clinical staff, which collects information from hospitals across the north of England to monitor health outcomes for mothers and babies. The project administrator contacts participants who still meet the criteria for inclusion in their third trimester to arrange a telephone interview with the project manager (GW). In the interview, the project manager will administer the 7-day TLFB questionnaire, the EQ-5D-3 L, and a NHS service use questionnaire. We will also check whether participant follow-up rates vary based on socio-economic profile and drinking status.

At 6 months after the due birth date of the participant, the project manager will again contact the RMSO to check whether the participant has experienced a stillbirth or loss after birth, and any such cases will be excluded from follow-up data collection without further contact. Birth outcome data (covering birth weight, gestational age at delivery, presence of congenital anomaly and fetal loss, or loss after birth if appropriate) will also be abstracted and recorded on a case report form. The project manager will then follow up eligible participants by telephone to ascertain longer-term follow-up rates. The screening and outcome measurement tools (the TLFB, EQ-5D-3 L & NHS service use questionnaires) will be re-administered, and open response questions will be asked about the acceptability of the instruments.

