**Methods:**

The trial will rehearse the parallel-group, non-blinded design and procedures of a subsequent definitive trial. Over 8 months, women aged 18 years and over (target number 2,742) attending their booking appointment with a community midwife (n = 31) in north-east England will be screened for alcohol consumption using the consumption questions of the Alcohol Use Disorders Identification Test (AUDIT-C). Those screening positive, without a history of substance use or alcohol dependence, with no pregnancy complication, and able to give informed consent, will be invited to participate in the trial (target number 120). Midwives will be randomized in a 1:1 ratio to deliver either treatment as usual (control) or structured brief advice and referral for a 20-minute motivational interviewing session with an alcohol health worker (intervention). As well as demographic and health information, baseline measures will include two 7-day time line follow-back questionnaires and the EuroQoL EQ-5D-3 L questionnaire. Measures will be repeated in telephone follow-ups in the third trimester and at 6 months post-partum, when a questionnaire on use of National Health Service and social care resources will also be completed. Information on pregnancy outcomes and stillbirths will be accessed from central health service records before the follow-ups. Primary outcomes will be rates of eligibility, recruitment, intervention delivery, and retention in the study population, to inform power calculations for a definitive trial. The health-economics component will establish how cost-effectiveness will be assessed, and examine which data on health service resource use should be collected in a main trial. Participants’ views on instruments and procedures will be sought to confirm their acceptability.

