## Methods/Design

### Setting

The trial setting is that of community antenatal care. Under National Health Service (NHS) antenatal care in the UK [31], women initially receive advice from a general practitioner (GP) or midwife about lifestyle, folic-acid supplements, food hygiene, and antenatal screening. A booking appointment subsequently takes place during the first trimester at the woman’s home or in a clinic at the GP surgery. At this meeting, the community midwife provides more detailed information on fetal development, procedures, and resources; carries out assessments to develop an individual care plan; and offers lifestyle advice, screening tests, and an ultrasound scan (carried out at 18 to 20 weeks if desired). Appointments then take place every 2 to 3 weeks from week 25 of pregnancy, in which the midwife carries out routine tests and offers staged advice as appropriate.

For this study, midwives (n = 31) working from four bases of a community midwifery service are recruiting patients over an 8-month period from January 2012. Between them, these midwives provide antenatal care for 36 general practices in Newcastle upon Tyne in north-east England (population 2,607,000; annual live births 30,826), a geographical area with high rates of alcohol misuse and a culture of heavy drinking [32-34]. The practices comprise 41 branch surgeries with diverse patient profiles (total list size 282,034). Each practice is served by one to three midwives and midwives may routinely provide care to patients at one to three practices, depending on practice list sizes and whether or not the midwife works full-time.

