#### Inclusion criteria

Any woman aged 18 years or above attending for her routine antenatal care appointment before 16 weeks of gestation who can and does provide verbal agreement to be screened for alcohol, who screens positive for risky alcohol use during pregnancy (score of three or higher on the consumption domain of AUDIT (AUDIT-C)) [35], and who can and does give written consent to participate in the research will be eligible for inclusion.

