### Interventions

#### Control condition: treatment as usual

Women in the control condition will receive usual care delivered by the midwife. This involves the midwife verbally advising that abstinence from alcohol during pregnancy is recommended, and supplying a copy of the Department of Health booklet *The Pregnancy Book*[37], an advisory publication that is issued to all women in the UK attending booking appointments and that contains advice about alcohol use during pregnancy (on page 32). If the midwife judges the reported rate of binge drinking or current alcohol consumption to be of concern, a referral is made to a drug and alcohol midwife for further assessment, advice, or treatment.

Treatment as usual is delivered at the booking appointment immediately after screening, obtaining written consent, and completing the research questionnaire.

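### The six-month interval to the first follow-up conflicts with its third-trimester label for women booked from 14 weeks, and reaches term for those booked from 11 weeks

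*Protocol article*

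**What the plan says.** All references are to the protocol article.

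- **Eligibility (Inclusion criteria):** a woman qualifies when "attending for her routine antenatal care appointment before 16 weeks of gestation".
- **Usual time of booking (Setting):** "A booking appointment subsequently takes place during the first trimester".
- **Baseline is the booking visit (Control condition):** "Treatment as usual is delivered at the booking appointment immediately after screening, obtaining written consent, and completing the research questionnaire". The brief intervention section has the same sequence.
- **First follow-up check (Follow-up):** "Six months after a baseline interview (during the third trimester), the project manager ascertains whether the participant has experienced a fetal loss". The check uses the regional maternity register and the community midwife. It covers fetal loss and pregnancy complications.
- **Contact after the check (Follow-up):** the project administrator "contacts participants who still meet the criteria for inclusion in their third trimester to arrange a telephone interview". At that interview "the project manager will administer the 7-day TLFB questionnaire, the EQ-5D-3 L, and a NHS service use questionnaire".
- **Abstract:** "Measures will be repeated in telephone follow-ups in the third trimester and at 6 months post-partum".
- **Outcomes proposed for the full trial (Measures, Baseline):** the list has "secondary outcomes including alcohol abstinence (binary) in the third trimester and 6 months post-partum". The planned primary outcome is the maximum number of units per drinking occasion during the pregnancy.
- **Missed interviews (Participant compliance):** up to two further calls, to rearrange within one week.
- **Second follow-up (Follow-up):** timed from the due date, at six months after it.

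**The concern.** The first follow-up has two anchors: a fixed interval from baseline and a stage of pregnancy. They agree only if the baseline is early enough in gestation, and the inclusion limit allows baselines that are not.

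The measurement at stake is a diary of the preceding seven days. If it is completed after birth, it describes postnatal drinking, partly or wholly. It is then not a third-trimester observation, although abstinence is to be reported for that period and the pilot is meant to supply variability estimates for the definitive trial. The EQ-5D response taken at the same call enters the rehearsal of the QALY calculation.

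Retention is a primary outcome of the pilot, and 67% at the first follow-up is one of the stated criteria for continuing. Calls that fall around the due date or soon after a birth may go unanswered for reasons that come from the schedule and say little about whether the trial is feasible.

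The text also seems to assume that nobody has delivered by the first check. Loss after birth is named only at the second check, and the first check exists to avoid distressing contact.

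**Working it through.** **Inputs from the protocol article.** Latest baseline: 15+6 weeks (Inclusion criteria). Interval: six months (Follow-up). Rearrangement of a missed interview: up to one week (Participant compliance).

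**Assumptions not in the article.** Due date at 40 weeks; term from 37 weeks; six calendar months = 365.25 / 2 / 7 = 26.09 weeks, rounded to 26. The earliest baseline shown, 8 weeks, is illustrative.

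**Formula.** Gestation at the check = gestation at baseline + 26 weeks.

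**The plan's own equation first (six months after baseline = third trimester).** For first-trimester baselines it reproduces: 8 + 26 = 34 weeks and 13 + 26 = 39 weeks, both late pregnancy and before the due date.

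**Across the eligibility window:**

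| Baseline (weeks) | Check at (weeks) |
|---|---|
| 8+0 | 34+0 |
| 10+0 | 36+0 |
| 11+0 | 37+0 |
| 12+0 | 38+0 |
| 13+0 | 39+0 |
| 13+6 | 39+6 |
| 14+0 | 40+0 |
| 15+0 | 41+0 |
| 15+6 | 41+6 |

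**Thresholds.** For the check to fall before 40 weeks, baseline must be before 40 − 26 = 14 weeks. For it to fall before 37 weeks, baseline must be before 37 − 26 = 11 weeks.

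**From check to interview.** Only women who pass the check are contacted, and an interview is then arranged. The times above are therefore the earliest possible interview times under the six-month rule. If a missed interview is rearranged a full week later, a baseline at 13+0 gives 13 + 26 + 1 = 40 weeks.

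**Sensitivity to the length of six months.** With six 4-week months (24 weeks), the latest baseline gives 15+6 + 24 = 39+6 weeks, one day before the due date. A baseline at 13+0 gives 37 weeks. On this lenient reading the check stays before the due date, but the latest bookers have almost no time left to arrange a call.

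**Scale of the retention criterion.** The planned 120 recruits × 0.67 = 80.4 women at the first follow-up. Each woman missed moves the observed rate by 1 / 120 = 0.83 percentage points. How many would be missed because of timing cannot be derived from the article.

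**The case against.** A reader might infer that the first follow-up is partly a post-delivery measurement that records the wrong period, that the variance of the outcome is inflated, and that retention will look worse than it should. The article does not support this.

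- **The six-month clause times the check.** It carries its own third-trimester qualifier, and the contact clause separately places the approach to the woman in the third trimester, as does the abstract. This stands: the text does not establish that interviews take place after delivery. It does not remove the conflict, because the steps are sequential. With a baseline from 14 weeks, both rules can be met only if the woman is undelivered at or beyond her due date.
- **Past the due date is not the same as delivered.** This stands in both directions: a woman at 41 weeks may still be pregnant, and one at 38 weeks may not be.
- **Booking is described as a first-trimester visit.** This stands, so it would be wrong to say that the anchors agree only for early bookers. The outright conflict lies in the last two weeks of eligibility. Between 11+0 and 13+6 weeks the point is only that some women may have delivered.
- **The effects on variance and retention have no figure behind them.** This stands; they are plausible but not shown. The pilot tests no hypothesis, and abstinence is a secondary outcome of a later trial. The second continuation criterion also lets the team proceed if feasible changes to procedures would achieve the rates, and a new schedule is such a change.
- **Later data could identify misplaced interviews.** Gestational age at delivery is abstracted at the second follow-up and could be set against the interview date. That would flag such interviews but would not recover the missing third-trimester observation.
- **A condensed article may leave a gestational window to the full protocol.** This would answer a complaint about missing detail. Here two stated rules disagree.

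**Conclusion.** The concern holds as a conflict between stated rules. With six months taken as 26 weeks and a due date at 40 weeks, baselines at 14+0 to 15+6 put the first check at 40+0 to 41+6 weeks, so the interval and the third-trimester label cannot both be reliably met for these women. Baselines at 11+0 to 13+6 put it at 37+0 to 39+6. That agrees with the label for women still pregnant, but some may have delivered.

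The consequences apply only to women who have delivered or are about to, and they are possibilities: a diary and EQ-5D that may cover postnatal days, a mistimed abstinence measure, and a first-wave retention rate that may be lowered by the schedule. How many of the planned 120 women are affected is unknown. The point still merits correction, because it touches a continuation criterion and an outcome that the pilot is meant to rehearse.

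**What to change.** Replace the fixed six-month interval with a schedule set by gestational age or due date, so that the check and the interview both fall in the third trimester and before term. The second follow-up already uses the due date, so the information is to hand.

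- Keep the register and midwife check shortly before each call. A single check followed by a wide interview window would let a loss or complication arise unseen in between.
- Record gestation and delivery status at interview.
- Do not count interviews held after delivery as third-trimester outcomes. Report them separately.

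An interview window of 31 to 36 weeks is one example; the article gives no basis for a particular window.

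**Cost.** A changed scheduling rule and a small addition to the interview form. The interval from intervention to interview becomes generally shorter and more variable. With the example window, a woman with a baseline at 15+6 weeks would be interviewed 15+1 to 20+1 weeks later (31+0 − 15+6 and 36+0 − 15+6). One with an assumed baseline at 8 weeks would be interviewed 23 to 28 weeks later. The present rule gives about 26 weeks for everyone. The interval should be recorded so that it can be described alongside the outcome.
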